### Hypotheses

The specific hypotheses to be tested include the following. In infants born very preterm:A strong correlation exists between MRI, clinical measures and perinatal variables at 30 weeks PMA.Brain structure and function at 30 weeks PMA predicts outcomes at 40 weeks PMA, 3 months CA and 12 months CA.Brain structure and function at 40 weeks PMA predicts neurodevelopmental outcome at 3 and 12 months CA.A strong correlation exists between EEG, clinical measures and perinatal variables at 40 weeks PMA, and 3 months and 12 months CA.

## Methods and analyses

### Design

A prospective observational cohort study of infants born very preterm with a comparison group of infants born at term.

### Ethical considerations

Ethical permission to conduct the study has been obtained from the Human Research Ethics Committees at The Royal Brisbane & Women’s Hospital (HREC/12/QRBW/245), and The University of Queensland (2012001060). The trial has been registered with the Australian New Zealand Clinical Trials Registry (ACTRN12613000280707). Participation in the study is voluntary, written informed consent for participation in the study is obtained from a parent or guardian, and families may withdraw from the study at any time without explanation.

## Study sample and recruitment

### Preterm sample

This study aims to recruit 80 preterm infants from the Neonatal Intensive Care Unit (NICU) at the Royal Brisbane and Women’s Hospital (RBWH). A research nurse will screen infant admissions for eligibility, and determine the appropriate stage to approach the family based on medical stability and approval from the treating neonatologist. Eligible families will be approached and if they express an interest in the study, they will be provided with detailed information and an explanation of the study. Parents will be given the opportunity to ask questions and discuss involvement with their treating clinician prior to making their decision. Informed written consent will be obtained from parents or guardians interested in participating and their infant will be formally enrolled.

### Inclusion criteria

Infants born at ≤30 week’s gestation, who live within 200 km of the hospital to allow for follow up hospital appointments and home visits, and have English speaking families as there is insufficient funding for translators, are eligible for this study.

### Exclusion criteria

Infants diagnosed with any congenital or chromosomal abnormality that could adversely impact neurodevelopmental outcome, and/or any contraindications to MRI, are ineligible for this study.

### Term reference sample

Twenty term born babies will be recruited from either the postnatal ward of the RBWH, or as interested volunteers by word of mouth.

### Eligibility criteria

Infants are eligible to participate in the reference sample if they are born between 38 and 41 weeks gestation following an uncomplicated pregnancy and delivery, have a birth weight above the 10th percentile, and are not admitted to neonatal intensive or special care units following their birth.

### Sample size

There are no data currently available to assess the relationship between MRI and clinical measures at 30 weeks PMA to predict motor outcome at 3 months CA and motor/neurodevelopmental outcome or CP at 12 months CA. Sample size calculations are based on a study investigating the ability of MRI at TEA, and the GMs assessment, to predict motor outcomes and CP at 12 months CA [6]. In a prospective cohort of infants born <30 weeks GA and in a total sample size of *n* = 86, MRI was classified as normal (*n* = 22), or with mild (*n* = 54), moderate (*n* = 6) or severe (*n* = 4) white matter abnormality (WMA) [93]. Infants with normal or mild WMA were grouped (*n* = 76), and infants with moderate and severe WMA were grouped (*n* = 10) [6]. We assume the same ratio (7.6 MRI normal or with mild/moderate WMA: 1 MRI with moderate/severe WMA) will be observed in this study. Of the *n* = 10 infants in the prior study that had moderate/severe WMA, *n* = 5 (50 %) developed CP [6]. If we assume that 5 % of infants with MRI normal or with mild/moderate WMA develop CP, then the study requires 69 infants to be recruited (8 with MRI with moderate/severe WMA and 61 with MRI normal or with mild/moderate WMA) in order to be able to reject the null hypothesis that the proportion of infants with CP in the two groups are equal with power = 90 %. The Type I error probability associated with this test of this null hypothesis is 0.05. In order to explore WMA earlier, at 30 weeks PMA, and its ability to predict CP at 12 months CA, an increase in the projected numbers will be required, and a further 15–20 % added to account for attrition. Consequently, the aim is to recruit a total sample size of 80 infants with full data sets.

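### The step from 69 required infants to a target of 80 covers a 15 % attrition mark-up only, leaves nothing for the 30-week increase, and uses 80 both as recruited and as complete

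*Protocol article*

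**What the plan says.** All but one of these statements are in the Protocol article, Sample size section.

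- **Basis.** An earlier cohort of 86 infants had MRI at term-equivalent age: 22 normal, 54 mild, 6 moderate and 4 severe WMA. The source grouping is given as "Infants with normal or mild WMA were grouped" (76), against moderate and severe together (10).
- **Assumptions.** Cerebral palsy (CP) in 50 % of the smaller group, from 5 of the 10 "infants in the prior study that had moderate/severe WMA", and in 5 % of the larger group. The ratio is written as "7.6 MRI normal or with mild/moderate WMA: 1 MRI with moderate/severe WMA".
- **Test.** The aim is to reject the hypothesis that "the proportion of infants with CP in the two groups are equal with power = 90" per cent. "The Type I error probability associated with this test of this null hypothesis is 0.05". Neither the test nor its sidedness is named.
- **Result.** 69 infants, 8 and 61.
- **Additions.** For WMA at 30 weeks, "an increase in the projected numbers will be required, and a further 15–20 % added to account for attrition".
- **Target.** "Consequently, the aim is to recruit a total sample size of 80 infants with full data sets".

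The Preterm sample section says: "This study aims to recruit 80 preterm infants from the Neonatal Intensive Care Unit". The abstract also gives 80 preterm infants as the number to recruit, with the 20 term infants counted separately.

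**The concern.** The section names two separate additions to 69, one for the 30-week question and a further one for attrition. The whole margin is 80 − 69 = 11 infants, too few to serve both purposes.

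The number 80 also has two meanings: infants enrolled in the abstract and the recruitment section, and infants with full data in the sample size section. Both can be true only if nobody is lost, yet the plan expects to lose 15–20 %.

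At stake is how the power claim is read. A reader would take 90 % power as delivered by 80 recruits and as extending to 30-week MRI. The plan's figures support neither.

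**Working it through.** **Inputs** (Sample size section): CP proportions p1 = 0.50 and p2 = 0.05; ratio k = 76/10 = 7.6; type I error 0.05; power 0.90; attrition 15–20 %. Two-sidedness is an assumption; the one-sided version of the formula below gives a total of 59.0, not 69.

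**1. Reproduce 69.** Pooled two-proportion formula without continuity correction:

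n1 = [1.960·√(p̄(1−p̄)(1+1/k)) + 1.2816·√(p1(1−p1) + p2(1−p2)/k)]² / (p1−p2)²

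- p̄ = (0.50 + 7.6 × 0.05)/8.6 = 0.1023
- first term: 1.960 × √0.10394 = 0.6319
- second term: 1.2816 × √0.25625 = 0.6487
- n1 = (0.6319 + 0.6487)²/0.45² = 8.10; total = 8.6 × 8.10 = 69.6

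This agrees with the stated 69. Power at 8 v 61 is 89.7 %.

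**2. What 80 contains.**

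- 80/69 = 1.159
- mark-up on 69: 69 × 1.15 = 79.4 (80 rounded up); 69 × 1.20 = 82.8 (83)
- inflation by N/(1 − d): 69/0.85 = 81.2 (82); 69/0.80 = 86.3 (87)

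A simple 15 % mark-up uses the whole margin. A simple 20 % mark-up already exceeds 80, and so do both figures obtained by division. All of this is before any 30-week increase.

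**3. Reading A: 80 recruited.**

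- 80 × 0.85 = 68 and 80 × 0.80 = 64 complete, both below 69
- largest loss that keeps 69: 1 − 69/80 = 13.75 %, less than the plan's lower figure

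**4. Reading B: 80 complete.** Recruitment would be 80/0.85 = 94.1 (95) to 80/0.80 = 100, against the stated 80.

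**5. Power on each reading**, with the same formula, n1 = N/8.6 and power = Φ[(0.45·√n1 − 0.6319)/0.5062]:

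| N complete | n1 | Power |
|---|---|---|
| 64 | 7.44 | 88.0 % |
| 68 | 7.91 | 89.5 % |
| 69 | 8.02 | 89.8 % |
| 80 | 9.30 | 92.8 % |

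Against 89.8 % at 69, attrition costs 0.3 to 1.8 percentage points.

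**6. Group labels.** Normal/mild against moderate/severe is (22 + 54):(6 + 4) = 76:10 = 7.6:1. The larger group's later label, mild/moderate, puts moderate WMA in both groups. The counts, the ratio and the 8 + 61 split all match mild.

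**The case against.** **The shortfall hardly matters.** By the formula that reproduces 69, power stays at 88.0–89.5 %. Exact power of the uncorrected chi-squared test is 92.1 % at 8 v 60, 90.3 % at 8 v 56, 88.6 % at 7 v 57 and 87.9 % at 7 v 61. This stands: attrition alone does not undermine the term-age comparison.

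**The target sentence says full data sets, so 80 may mean completers.** On that reading the 11 extra infants could be the 30-week increase, and power is adequate. But attrition is then missing from the recruitment figure, which the abstract and the recruitment section fix at 80. The inconsistency moves; it does not go away.

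**No 30-week data existed, so the increase could not readily be sized.** The section opens by saying so, and it is a fair reason to claim no formal power. It is not a reason to call an increase necessary and then leave it out.

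**Some details are inferred.** The article describes the 69 as infants to be recruited. Treating them as infants with an observed outcome follows from adding attrition afterwards. The article does not show how 80 was reached, so a reader might infer multiplication in place of division, but cannot establish it.

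**Two stronger readings are not supported.** A reader might infer serious underpowering from Fisher's exact test, which gives 79.1 % at 7 v 57 and 85.9 % at 8 v 60. But the plan names no test, and Fisher gives 85.7 % even at the full 8 v 61, so its level mainly reflects the choice of test. A reader might also infer from the overlapping labels that only severe WMA forms the small group. The section always keeps moderate WMA in that group and fixes it by n = 10, by 7.6:1 and by 8 + 61.

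**Conclusion.** The point holds, at modest size. The figure of 69 is sound; the step to 80 is not. The margin equals a 15 % mark-up on 69 and contains nothing for 30 weeks. Recruiting 80 leaves 64–68 infants and power of about 88–89 %. Having 80 complete gives about 93 % but needs 95–100 recruits, which contradicts the recruitment target.

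The weightier part is the 30-week increase, since the only power figure concerns term-age MRI. That is not to say that 30-week MRI is the study's single main question: the Primary aims cover both 30 and 40 weeks.

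The power figures assume CP in 50 % and 5 %, a 7.6:1 ratio, the plan's 15–20 % attrition falling equally on both groups, and an uncorrected two-sided two-proportion test. The label overlap is editorial and changes no number. This should be corrected, but it does not put the study's conduct in doubt.

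**What to change.** Replace the end of the Sample size section, from the 30-week sentence on, with text such as:

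> We will recruit 80 preterm infants and, with 15–20 % attrition, expect 64–68 to have complete data. This gives about 88–89 % power (uncorrected two-proportion test, two-sided 0.05) for the comparison of CP between normal/mild and moderate/severe WMA on term-age MRI. No formal power is claimed for MRI at 30 weeks.

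Three further points:

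- Delete the phrase about full data sets. If 80 complete infants are really meant, recruitment must instead become 95–100 in the abstract and the Preterm sample section.
- Remove the statement that numbers must rise for 30 weeks. If it stays beside the disclaimer, the contradiction remains.
- Change mild/moderate to mild wherever it labels the larger group.

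The cost is wording only. Recruitment of 80 is unchanged, and the stated power becomes slightly less favourable.

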### Perinatal data collection

An extensive record of the pregnancy, birth history, and neonatal course will be collected from the medical discharge summary. This will allow detailed description of the characteristics of the sample, allow comparison to outcomes establishing predictor variables, and to adjust for confounders.

A number of prenatal variables have been shown to impact short and long-term outcomes. Prolonged rupture of membranes, defined as spontaneous rupture of membranes ≥24 h before delivery is the most significant risk factor of a poor outcome among pregnancy history [94, 95]. Maternal antenatal corticosteroid administration reduces the risk of neonatal death and respiratory distress (complete course defined as more than 1 dose of steroids given, and 1st dose at more than 24 h and less than 8 days before birth) [94–96]. Evidence also exists for antenatal steroids protecting against cerebral haemorrhage [97]. The neuroprotective effect of magnesium sulphate administration reduces the risk of an outcome of CP (relative risk 0.68, 95 % confidence interval 0.54 to 0.87) [98]. Assisted conception is associated with adverse neurodevelopmental outcomes independent of prematurity, multiple pregnancy and gender for infants born between 22–26 weeks gestation [99]. Multiple birth status will be examined as the widely held view that singletons experience better outcomes than multiples has recently been challenged. In a population based study of *n* = 1473 born <29 weeks gestation, infants from multiple gestation pregnancies demonstrated comparable neurodevelopmental outcomes to singletons [100].

Birth history variables collected will include GA at birth, gender and birthweight. The risk of CP and adverse neurodevelopmental outcomes increases with decreasing GA at birth [101] and multiple studies report poorer outcomes for male infants [94, 102–104]. Intra uterine growth retardation (IUGR) can result in decreased cortical volume, poorer outcomes and increased risk of neonatal complications [105, 106] and babies that are small for gestational age (SGA) are at a higher risk of death, adverse neonatal outcomes and neurodevelopmental impairment [107]. Growth restriction in this study will be defined as a birth weight <10th percentile based on the Olsen growth curves.

Information will be gathered over each infant’s neonatal course from birth until discharge from hospital. Cranial ultrasound findings, specifically findings of PVL and IVH graded according to the criteria of Papile et al., 1978 will be documented, with higher grades predictive of adverse outcomes and CP [108]. Necrotising enterocolitis (NEC) is associated with poorer growth, cognitive and motor outcomes and is considered proven if the infant warranted treatment which included nil by mouth and antibiotics [95, 109]. Late onset sepsis is a significant risk factor, diagnosed by isolation of an organism from at least one blood culture and a decision to give antibiotics with therapeutic intent, from 48 hrs after birth [94, 95]. Culture proven sepsis is independently associated with an outcome of CP [110]. Postnatal corticosteroid use demonstrates an independent effect on poor outcome, in particular with behavioural outcomes and CP [94, 111, 112]. Bronchopulmonary dysplasia or chronic neonatal lung disease are independent risk factors for adverse neurodevelopmental outcomes due to recurrent episodes of hypoxia [111, 113–117]. Chronic neonatal lung disease is defined as babies born <32 weeks GA requiring any respiratory support or supplemental oxygen for a chronic pulmonary disorder at 36 weeks PMA [95]. Postmenstrual age at NICU discharge will be documented, as poorer behavioural outcomes are associated with longer length of hospital stay [118].

For each infant from birth until 34 weeks PMA, the daily intake of all nutrient-containing solutions will be recorded. Intake of protein, lipid, carbohydrate and energy for each day will be calculated by multiplying intake volumes for each solution administered by the nutrient concentration obtained from manufacturers specifications or, for breast milk, published data [119].

Socio-demographic information such as maternal and paternal education and occupation will be collected using a baseline parent questionnaire (see Additional file 1). Social and environmental factors may impact infant development, and low socio-economic status and parenting factors have been shown to adversely influence outcomes [120]. Social risk will be assessed using a score measuring six aspects of social status including: family structure, education of primary caregiver, occupation of primary income earner, employment status of primary income earner, language spoken at home and maternal age [116, 121, 122]. Each item will be scored between 0 and 2 for a total score of 12, with scores of 2 and above being considered high social risk in line with other research in this population [121, 122]. Higher social risk has been strongly associated with later behaviour problems, and independently predicts a lack of early intervention services [122, 123]. A recent systematic review found evidence that lower socio-economic status results in an additional risk of CP, over and above the risks conferred by prematurity or lower birthweight [124].

### Procedures

Study procedures are depicted in Fig. 1. Participants will be recruited, consented and enrolled as described above. Between 30–32 weeks PMA, when medically stable, infants will undergo an MRI. In the event an MRI cannot be undertaken due to medical instability, MRI’s will be conducted when the infant becomes medically stable and up to a maximum age of 36 weeks PMA. This will ensure that less fragile infants are not over-represented in the sample. The following day, infants will undergo clinical assessment by an assessor blinded to GA at birth, CUS and MRI findings and any unrelated medical information, and a video recording of their spontaneous movements will be captured. As there are no established gold standard neurological or neurobehavioural assessments for use at this time point, a combination of the NICU Neonatal Neurobehavioural Scale (NNNS), Hammersmith Neonatal Neurological Examination (HNNE), and the Premie-Neuro will be used [125]. These assessments will be combined to minimise handling and modified to remove items unsuitable for administration at this age. The assessment time will be 10–15 min, conducted before a scheduled feed and cares to ensure optimum comfort and alertness. Infant cues, physiological signs of stress or distress, oxygen saturations and heart rate will be monitored throughout, and the assessment paused or discontinued where necessary. The assessment will be video recorded for independent scoring and testing of inter- and intra-rater reliability.

**Fig. 1 Fig1:**
[figure not shown]
Consort Flowchart of PPREMO Study Procedure

At TEA the family will be invited to return for their infant to undergo a second MRI and an EEG. The following day an assessor blinded to GA at birth and CUS and MRI findings will visit the family at home to undertake the clinical assessments. A video of the infant’s spontaneous movement will be recorded for later scoring of the GMs assessment, a brief assessment of visual function will be undertaken and 3 motor and neurobehavioural assessments will be administered, combined to remove duplicate items. The NNNS assessment, which is highly structured, will be completed first, followed by the few additional items of the HNNE and the Test of Infant Motor Performance (TIMP). Total assessment time will be approximately 1 h, however, the assessment will be conducted at the infant’s pace, and breaks for feeds or sleep will be undertaken as appropriate.

At 3 months CA, during a home visit, a GMs video of the infant’s spontaneous movement will be taken, and a visual assessment and the TIMP will be completed. The total assessment time will be approximately 40 min.

At 12 months CA, families will be invited back to the RBWH for follow up assessment of their child’s motor and neurodevelopmental outcome. In a telephone call prior to the appointment a research nurse will gather up to date information on the child’s current medical team, medical history since discharge, any diagnoses made and details of any interventions they have received. A paediatrician blinded to medical history will assess for signs of neurological abnormality and the presence of features of CP. A physiotherapist blinded to background history will conduct neurodevelopmental and motor assessments. As no single measure has been shown to provide conclusive data on attainment and quality of motor skills in this population, a combination of the Bayley Scales of Infant and Toddler Development III (Bayley III), the Neurosensory Motor Developmental Assessment (NSMDA) and the Alberta Infant Motor Scale (AIMS) will be performed [126]. The total assessment time will be 1–1.5 h.

## Measures

### MRI methods

#### Image acquisition

Brain MRI will be performed using a 3T (Siemens Tim Trio, Erlangen, Germany) and an MR compatible incubator with dedicated neonatal head coil (LMT Lammers Medical Technology, Lubeck, Germany). Noise from the MRI will be attenuated using Natus Mini Muffs (Natus Medical Inc., San Carlos, CA). The preterm group will have an MRI at 30–32 and again at 40–42 weeks PMA. The term group will have an MRI at 40–42 weeks PMA. All infants will be monitored with pulse oximetry and electrocardiographic monitoring. Infants will be fed, fitted with ear protection to minimize noise exposure, carefully wrapped and placed in the incubator in the scanner without sedation or anaesthesia. The total scanning duration will be approximately 45–60 min for each baby. Where possible, images impacted by significant motion artefacts will be rescanned. The MR protocol will include T1, T2 TSE, T1w MPRage, T2w HASTE and 3 echo T2 map, Arterial Spin Labelling (ASL), 30 direction diffusion weighted imaging (DWI), and 64 direction DWI sequences. Additional file 2 outlines the MRI protocol parameters. A neuroradiologist will review clinical sequences and classify white and grey matter injury [93, 127].

Quantitative T2 will be measured using a T2 image series acquired with echo times of 27, 122 and 189 ms and repetition time 10580 ms; 47 axial contiguous slices of 2.0 mm thickness will be acquired with a 144 × 180 mm field of view, a flip angle of 150°, and a 153 × 256 matrix (reconstructed to 204 × 256), resulting in voxel sizes of 0.70 × 0.70 × 2.0 mm^3^. T1-weighted magnetization prepared rapid-acquisition gradient echo volumes in the sagittal plane will be acquired with an echo time of 3.21 ms and repetition time 2100 ms; 96 sagittal slices of 1.3 mm thickness will be acquired with a 160 mm field of view, a flip angle of 9°, and a 128 × 128 matrix, resulting in voxel sizes of 1.25 × 1.25 × 1.3 mm^3^.

Diffusion images will be acquired using single-shot echo planar multi-direction diffusion-weighted sequence, employing dual bipolar diffusion gradient and double spin. This will include the acquisition of a 30 direction DWI protocol (b = 1000 s/mm^2^) and a 64 direction HARDI protocol (b = 2000 s/mm^2^). The images will be acquired per location, consisting of one low (b = 0 s/mm^2^) and the rest high (b = 1000 or 2000 s/mm^2^) diffusion-weighted images, in which the encoding gradients are uniformly distributed in space. Imaging parameters of the diffusion sequence will be: field of view 224 × 224 mm, matrix 128 × 128, repetition time 9500 ms, echo time 130 ms and flip angle of 90°. A field map for diffusion data is acquired using two 2D gradient recalled echo images (TE1/TE2 4.9/7.4 ms) to assist in correction for residual distortions due to susceptibility inhomogeneity’s (acquisition time 1 m). These sequences allow exploration of brain microstructure and function, specifically: (i) regional and global cortical surface and thickness, (ii) white matter organisation, (iii) structural connectivity of relevant areas and (iv) pre-myelination (T2).

Arterial spin labelling MRI provides a non-invasive technique to measure cerebral blood flow (CBF), although its feasibility and value in neonates is largely unknown. As the neonate’s brain rapidly grows, it is anticipated that an associated increase in CBF would occur to supply the nutrients and energy needed for the added brain weight [128]. Arterial spin labelling MRI will be performed using a PICORE Q2TIPS sequence with echo-planar imaging. Imaging parameters of the ASL scan will be: field of view 256 mm, matrix 64 × 64, repetition time 3427.5 ms, echo time 21 ms, inversion time of arterial spins (TI1) 700 ms, saturation stop time 1600 ms, total transit time of the spins (TI2) 1800 ms, tag thickness 100 mm, tag to proximal slice gap 25 mm, 17 axial slices, slice thickness 5 mm, time lag between slices 22.5 ms, and Bandwidth Per Pixel Phase Encoding time of 23.343 ms.

